### Data collection and management

All data will be acquired only by the members of the investigative team who are obligated to keep the data confidential from the public and only use the data for scientific research. The data will be documented in an exclusive computer as well as on paper. The data will be uploaded to an online data management team (ResMan® research manager repository, http://www.medresman.org) who will also oversee the trial process. To ensure confidentiality, user names and passwords will be assigned to the investigators. Two experimenters will independently conduct the statistical analyses. If there are more than one implant placed on one side, to avoid potential bias, only one random implant will be evaluated.

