### Inclusion criteria

The following are the inclusion criteria:
Bilateral first/second molars requiring extraction due to severe periodontal disease (i.e., prognosis regarded as “hopeless” [17]) and the patient’s desire for replacement with implantsResidual alveolar bone height of the compromised teeth ranging from 1 to 3 mmAge ≥ 18 yearsHealthy maxillary sinuses with intact sinus floorsGood general healthNon-smokersSigned informed consent formGood oral hygiene and compliance with the treatment regimen

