#### Primary outcomes of the trial

The primary parameter of the current trial is implant survival rate, which will be calculated as the proportion of retained implants at 5 years of follow-up.

The criteria of survival or failure of an implant were referred to the consensus of the International Congress of Oral Implantologists [20]. The implant will be regarded as failed if any of the following happens: (a) pain on function, (b) mobility, (c) radiographic bone loss > 1/2 length of the implant, (d) uncontrolled exudate, and (e) no longer in the mouth. Otherwise, the implant will be regarded as surviving.

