
### Sample size

The PASS sample size software (version 11.0; NCSS, LLC, East Kaysville, UT, USA) was used to estimate the sample size needed for the current study based on the following formula: *N* = (1/Q1 + 1/Q2) [(*Z*_*α*/2_ + *Z*_*β*_)*σ*/*δ*]^2^. As the primary parameter, the implant survival rate was used to estimate the sample size. The mean 5-year survival rate and standard error (SE) were calculated as described in a previous study [21] (survival rate after 5 years = 97.8%; mean of paired difference [*δ*] = 5.0%; SE [*σ*] = 5.0%) with significance criteria of *α* = 0.05 (error) and *β* = 0.10 (type II error). A two-tailed, non-inferiority analysis was performed. To reach a power of 90%, at least 16 patients (32 sites) should be included. Assuming a dropout rate of 20%, 20 patients (40 sites) were needed. Considering the cluster effect caused by the split-mouth design, we further enlarged the sample size to 25 patients (50 sites) for this trial.

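### Evaluating one random implant per side is unbiased but gives up precision that a side average would keep

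*Protocol article*

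**What the plan says.** The rule stands under Data collection and management: where a side has several implants, "only one random implant will be evaluated", and the reason given is to avoid bias.

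Sides with more than one implant are foreseen. The Inclusion criteria admit "Bilateral first/second molars requiring extraction due to severe periodontal disease", and the surgical sections allow for one tooth or several. How often this will happen is not given.

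The primary outcome is defined per implant. It is "calculated as the proportion of retained implants at 5 years of follow-up", and the failure criteria are worded for the single implant: "The implant will be regarded as failed if any of the following happens". Sample size counts sites (25 patients, 50 sites) and takes "survival rate after 5 years = 97.8"% from a previous study. Statistical analysis names Cox regression and Kaplan-Meier for implant survival, the paired t test for clinical parameters, marginal bone and vertical bone gain, and the paired Wilcoxon test for histomorphometry.

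The article does not say when the random implant is drawn, or whether the other implants are measured and recorded.

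**The concern.** One value per side is a sound aim in a split-mouth trial with paired tests. A random draw is one way to reach it, but it adds the chance of which implant was picked to the noise already in the data. Averaging the implants on a side reaches the same aim without that added noise.

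This matters because the trial is small and, on its own survival figure, will see about one implant failure in all. For marginal bone level, bone height and peri-implant measurements, the draw uses less information than the patients could supply. For the primary outcome, an implant lost beside the selected one would not enter the survival proportion.

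**Working it through.** **Figures in the plan.** The plan attaches no figure to this rule, so there is none to reproduce. (The sample-size formula with equal groups and σ/δ = 1 gives 4 × (1.960 + 1.282)² = 42.03 sites, not 32. That is a separate matter, and nothing below depends on it.)

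**Inputs.** 50 sites, 25 per arm, and 97.8% five-year survival (failure 2.2%), from Sample size. Assumed, because the document gives neither: s, the share of sides with two implants, and ρ, the correlation between two implants on one side.

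**Same target, variance never larger.** Given the implants on a side, the expected value of a random draw is their mean, so both estimate the same quantity. The variance of the draw equals the variance of the mean plus the spread within the side. Example: if one of two implants fails, the draw scores 0 or 1 with equal chance; the average scores 0.5 every time.

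**Size of the gain.** Per unit of implant variance, a drawn implant has variance 1 and the mean of two has (1 + ρ)/2. With every side weighted equally:

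effective sites = 50 / [(1 − s) + s(1 + ρ)/2]

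| s | ρ | denominator | effective sites | gain |
|---|---|---|---|---|
| 0.5 | 0 | 0.750 | 66.7 | +33% |
| 0.5 | 0.3 | 0.825 | 60.6 | +21% |
| 0.5 | 0.6 | 0.900 | 55.6 | +11% |
| 0.25 | 0 | 0.875 | 57.1 | +14% |
| 0.25 | 0.6 | 0.950 | 52.6 | +5% |

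At s = 0.5 and ρ = 0.3 the confidence interval is √0.825 = 0.91 times as wide, about 9% narrower. With s = 0 or ρ = 1 the denominator is 1 and the gain is nil. The formula treats sides as independent. If v is the denominator and c ≥ 0 (with c < v) the correlation between a patient's two sides, the gain for the paired difference is (1 − c)/(v − c), which is at least 1/v. So the table does not overstate it.

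**Why not simply analyse every implant with equal weight?** Its effective size is 50(1 + s)² / [(1 − s) + 2s(1 + ρ)].
- s = 0.5, ρ = 0.3: 112.5/1.8 = 62.5
- s = 0.25, ρ = 0.6: 78.125/1.55 = 50.4
- s = 0.25, ρ = 0.8: 78.125/1.65 = 47.3, worse than the stated rule

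The side average cannot fall below 50.

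**Primary outcome.** One implant per side gives 25 × 0.022 = 0.55 expected failures per arm, 1.1 in all, and a chance of 0.978⁵⁰ = 33% of seeing none (independence assumed). Counting every implant gives 1.1, 1.4, 1.65 or 2.2 expected failures in all for s = 0, 0.25, 0.5 or 1.

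Read the 5.0% difference as a non-inferiority margin, treat the arms as independent and use a normal approximation at two-sided 0.05. Power is then 23% with 25 effective sites per arm. At 60.6/2 = 30.3 per arm the standard error is √(2 × 0.022 × 0.978/30.3) = 0.0377, and power is Φ(0.05/0.0377 − 1.96), about 26%. With two implants on every side it is 32% at ρ = 0.3 and at most 40%, at ρ = 0.

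**The case against.** The strongest defence is that the rule is deliberate and valid. It gives an unbiased failure proportion, removes within-side clustering, matches a sample size counted in sites, and supplies what the paired tests require. All of that stands.

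It is also fair to say that an implant-level survival model is no clear improvement. Even with two implants on half the sides (37.5 per arm), the chance that at least one arm has no failure is 1 − (1 − 0.978^37.5)² = 68%, against 82% with one implant per side (independence assumed). A Cox hazard ratio cannot then be estimated, and a clustered variance on 25 patients with one or two events would be fragile. This argues against an implant-level model, not against side averages.

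Three stronger readings are tempting, and the documents do not support them:

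- A reader might infer that collected data are thrown away. The article says only that one implant is evaluated; it does not say that the others are examined or recorded.
- A reader might infer that failures are hidden and survival is flattered. If one of two implants fails, the draw does miss it half the time, but surviving implants are left out by the same draw, so the proportion is not biased.
- A reader might infer a gap in safety oversight. Complications are documented at every follow-up visit, and surgical failure and adverse events go to the monitoring committee (Follow-up assessment, Secondary parameters, Harms). Nothing limits these channels to the selected implant.

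**Conclusion.** The rule is valid but needlessly imprecise. For outcomes measured at each implant, side averages give about 21% more effective sites if half the sides carry two implants and the within-side correlation is 0.3. The range is 11% to 33% for correlations of 0.6 to 0, and about 5% to 14% if only a quarter of sides do. These figures rest on assumed values for both quantities, and the gain can be nil.

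For survival, the benefit is mainly complete reporting of very few events: 0 to 1.1 more expected failures over the whole trial. The change leaves the primary comparison underpowered.

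**What to change.** 1. Evaluate every study implant at each follow-up visit.
2. For marginal bone level, bone height and peri-implant clinical parameters, average the implants on a side and carry that one value into the planned paired test. Leave the biopsies as they are, since a second sample would need an extra procedure. Surgical duration and patient-reported scores do not belong to a single implant and are unaffected.
3. Report failures of all implants by arm. Alongside the planned survival analysis, give the side-level failure proportion, meaning failed implants divided by implants on that side. Counting a side as failed when any implant fails is a different quantity and should not replace it.
4. If the one-implant analysis is kept as a sensitivity analysis, make the draw at placement, before any outcome is known, and record it.

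The cost is the extra measurement of the second implant at visits the patients already attend, possibly with a further periapical film if one film does not take in both implants. The planned paired tests do not change.

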### Training and calibration

One expert ([name]) with more than 10 years of working experience will be appointed to conduct the MSFE procedure. He will also receive training with the modified MSFE procedure with the use of a dental simulation model to fully master the novel surgical procedure prior to meeting with the first patient.

Before the examination, two independent investigators, other than the operator, will perform the radiographic measurements and histological evaluations using instructional CBCT data and histological sections. Both investigators are medical practitioners with at least 3 years of working experience and will be trained to adequate levels of accuracy and reproducibility to guarantee conformity. Clinical parameters, VAS scores, complications, and surgical durations will be collected by one researcher with at least 3 years of working experience to assure consistency.

### Statistical analysis

For continuous data, such as clinical parameters, consistency between the two examiners will be assessed with the intra-class correlation coefficient. For descriptive data, consistency will be assessed using Cohen’s *k* statistic. Descriptive statistics include frequency values (absolute and relative values) and metric data (arithmetic mean, standard deviation, and median). The measured data will be expressed as the mean ± standard deviation or median (quartile spacing) and the enumerated data as percentages. Cox regression and Kaplan-Meier survival analysis will be conducted to evaluate the survival rate of implants. The incidence of complications will be compared using the *χ*^2^ test. The paired-samples *t* test will be applied to evaluate the VAS scores, clinical parameters, degree of marginal bone remodeling, and vertical bone gain of the test and control groups. Histomorphometric measurements of the biopsies of both groups will be compared using the non-parametric Wilcoxon test for paired samples. All statistical analyses will be performed using IBM SPSS Statistics for Windows, version 19.0. (IBM Corporation, Armonk, NY, USA). Two-sided probability (*p*) values of < 0.05 will be considered statistically significant.

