**Methods/design:**

The study cohort included 25 adult patients (50 surgery sites) recruited from Peking University Hospital and School of Stomatology who met the inclusion criteria. The two sides of each patient will be randomly divided into two groups: a test group-modified MSFE or a control group-standard MSFE. The surgical duration and patient-reported outcomes (visual analog scale for discomfort) will be documented. Clinical indicators, including implant survival rates, mucosal conditions, and complications, will be recorded every 6 months during the 5-year follow-up period. The volume of the alveolar bone and marginal bone level will be assessed radiographically (cone-beam CT and periapical films) every 6 months. Histological analysis of biopsy samples retrieved from both sides will be performed to evaluate the biological features of the bone.

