## Methods

### Overview

The proposed study is designed as a prospective single-center, split-mouth, randomized controlled trial. We plan to recruit 25 patients with severely periodontally compromised molars on both sides and in need of dental implant treatment in the atrophied posterior maxilla. The participants will be recruited by the research staff from Peking University Hospital and School of Stomatology (Beijing, China). All procedures, recalls, and analyses will be conducted at this hospital. The study protocol was approved by the Ethics Committee of Peking University Hospital and School of Stomatology (approval no. PKUSSIRB-201840191). The study has been registered with the International Clinical Trials Registry Platform (identifier no. ChiCTR1900020648).

The systemic health status of all participants will be qualified prior to treatment. All patients recruited for the study will receive standard periodontal initial therapy and periodontal maintenance at regular intervals. Once the clinical and periodontal health of the patient is confirmed, MSFE surgery will be performed. Prior to surgery, all patients will be assessed both clinically and radiographically. Initial bone height, bone quality, and alveolar width will be assessed by cone-beam computed tomography (CBCT).

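### The plan names unpaired methods for implant survival (Cox, Kaplan-Meier) and complications (chi-square) in a split-mouth trial, and a hazard ratio does not estimate the paired 5-year difference used for sizing

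*Protocol article*

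**What the plan says.** The Overview states the design: "The proposed study is designed as a prospective single-center, split-mouth, randomized controlled trial". The abstract gives the unit of randomisation: "The two sides of each patient will be randomly divided into two groups: a test group-modified MSFE or a control group-standard MSFE". Under Data collection and management, a side with several implants contributes one, chosen at random. Each patient therefore supplies one test and one control observation.

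The section on primary outcomes makes the endpoint a proportion at a fixed time in follow-up: "The primary parameter of the current trial is implant survival rate, which will be calculated as the proportion of retained implants at 5 years of" …

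The Sample size section sizes the trial on a paired difference, with "survival rate after 5 years = 97.8%; mean of paired difference [*δ*] = 5.0%; SE [*σ*] = 5.0"%, and calls the analysis non-inferiority. It then adds: "Considering the cluster effect caused by the split-mouth design, we further enlarged the sample size to 25 patients (50 sites) for this trial".

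The Statistical analysis section names the paired t test and the paired Wilcoxon test for the continuous and histological outcomes. For the primary outcome it says "Cox regression and Kaplan-Meier survival analysis will be conducted to evaluate the survival rate of implants". For complications it says "The incidence of complications will be compared using the" χ² test. No paired, clustered or stratified form is given for either.

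The Missing data section counts drop-outs as non-survival, and the Sample size section allows for 20% drop-out.

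**The concern.** There are two linked problems.

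1. **Variance.** One paragraph specifies pairing for some outcomes and omits it for the primary outcome and the main safety outcome. Ignoring the pairing leaves the marginal rates and Kaplan-Meier curves intact, but the standard error of the comparison is wrong. The Sample size section recognises the clustering and answers it with more patients. A larger sample does not turn an unpaired standard error into a paired one.
2. **Target.** The endpoint is a 5-year proportion and the sizing quantity is a paired difference in that proportion. A hazard ratio is neither, and no contrast of the 5-year proportions is named.

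At stake are the interval on which similarity of the two procedures would be judged, and the ability to see excess complications. The second matters because the Challenges section itself expects the sinus membrane to be harder to keep intact when the tooth is still in place.

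**Working it through.** **The plan's own figures.** The drop-out step reproduces: 16/0.8 = 20 patients. The step to 25 is a factor of 25/20 = 1.25, with no correlation stated. The starting 16 patients (32 sites) does not reproduce at 90% power: with δ = σ, 4 × (1.960 + 1.282)² = 42.0 sites, while 80% power gives 4 × (1.960 + 0.842)² = 31.4. That is a separate matter, and nothing below rests on it.

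**Variance.** Take n pairs with rate p on both sides and within-pair correlation φ.
- Unpaired variance of the difference: 2p(1−p)/n.
- Paired variance: 2p(1−p)(1−φ)/n.
- The unpaired standard error is too large by 1/√(1−φ): 1.20 at φ = 0.30 and 1.51 at φ = 0.56.

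**Complications.** The documents give no rates or correlations, so those below are assumptions. Each row is from 100,000 simulated trials of 25 pairs with a latent normal correlation r. At a 20% rate, r = 0.5 and 0.8 correspond to φ of about 0.30 and 0.56.

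| Rates | r | Chi-square | Mid-p McNemar | Exact McNemar |
|---|---|---|---|---|
| 20% vs 20% (size) | 0.5 | 2.4% | 3.0% | 1.1% |
| 20% vs 20% (size) | 0.8 | 0.6% | 1.4% | 0.4% |
| 40% vs 15% (power) | 0 | 53% | 47% | 37% |
| 40% vs 15% (power) | 0.3 | 54% | 54% | 43% |
| 40% vs 15% (power) | 0.5 | 54% | 61% | 48% |
| 40% vs 15% (power) | 0.8 | 53% | 73% | 58% |

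Repeat runs move the chi-square size at r = 0.8 between about 0.5% and 0.7%, and the powers by about a point.

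**Hazard ratio, implant failures only** (97.8% survival, 25 per side).
- Expected failures: 50 × 0.022 = 1.1.
- No failure on a given side: 0.978²⁵ = 0.573.
- No failure on at least one side, so no finite hazard ratio: 1 − (1 − 0.573)² = 0.818 if sides are independent. Simulation gives 79% and 73% at r = 0.5 and 0.8.
- No failure at all, independent sides: 0.978⁵⁰ = 0.329.

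**Hazard ratio, drop-outs counted as failures.** A lost patient adds an event to both sides. A side is then event-free only if nobody drops out, so for independent sides the probability is (1−d)²⁵ × 0.818:
- d = 5% (assumed): 0.277 × 0.818 = 23%.
- d = 10% (assumed): 0.072 × 0.818 = 6%.
- d = 20% (planned): 0.0038 × 0.818 = 0.3%.

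At 20%, drop-outs contribute 25 × 0.2 × 2 = 10 events, and the remaining 20 patients contribute 40 × 0.022 = 0.88. About 10 of 11 events are thus identical on both sides. They pull the ratio towards 1 and carry no information on treatment.

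**Effect on an interval.** Suppose there are five drop-outs and one further failure on one side, so 6/25 against 5/25.
- Unpaired 95% half-width: 1.96 × √(0.24×0.76/25 + 0.20×0.80/25) = 0.229, or ±23 points.
- Paired (Tango) interval for the 4-point difference: −10 to +20 points.

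**Limit of any remedy.** With no discordant pair at all, the Tango limits are ±z²/(n+z²) = ±3.84/28.84 = ±13 points, still wider than the 5.0 points in the Sample size section.

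**The case against.** - **Independence is not stated.** This stands. The protocol nowhere says that the two sides are treated as independent patients, and a fuller analysis plan, not shown, may settle the variance. But a section that specifies pairing for two tests and omits it for the others reads most naturally as unpaired for those others.
- **The hazard ratio.** From so few expected failures a reader might infer that the ratio will usually not exist, or that the primary comparison will yield no estimate. The documents do not support that. It is true only on implant failures alone; at the planned drop-out, the Missing data rule makes the ratio finite in more than 99% of trials. What remains is that the estimate is uninformative and off target.
- **No false positives.** A reader might take a wrong variance to mean inflated type I error. With positive correlation it is the reverse: the unpaired test is conservative.
- **The gain depends on the remedy.** This stands. Exact McNemar has less power than chi-square at r = 0.5 (48% against 54%) and gains only about 4 points at r = 0.8. Mid-p gains at 0.5 and above, and loses about 6 points at zero correlation.
- **Patient-stratified Cox is no rescue.** This stands. It needs discordant pairs in both directions, which are absent in about 83–95% of simulated trials at equal 97.8% survival.
- **Kaplan-Meier does estimate the endpoint.** This stands per arm: its 5-year value is the quantity wanted. Only the paired contrast between arms is missing.

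**Conclusion.** The point holds as a mismatch between design and analysis. The primary comparison and the complication comparison are named in unpaired form for 25 matched pairs, and the larger sample does not correct the variance. The consequence is lost precision and power, not false positives. For complications, size falls to about 2.4% or under 1% instead of 5%, and roughly 6 to 20 points of power are forgone against mid-p McNemar at latent correlations of 0.5 to 0.8. Nothing is gained at 0.3 or below. These figures rest on assumed rates and correlations.

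For the primary outcome, the hazard ratio does not estimate the 5-year proportion or the paired difference used for sizing. On implant failures alone it is not finite in 73–82% of trials, given the plan's 97.8% survival on both sides. At the planned 20% drop-out it is nearly always finite, but about ten in eleven of its events are drop-outs shared by both sides. The claim that no estimate will usually exist goes beyond the documents.

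**What to change.** In the Statistical analysis section:

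- Make the primary comparison the paired difference in 5-year implant survival, with a score (Tango) confidence interval read against the non-inferiority margin. Say explicitly whether the 5.0% in the Sample size section is that margin; the protocol calls it a mean paired difference.
- Keep Kaplan-Meier curves by arm as description.
- If a Cox model is kept, make it supportive only, with patient-clustered robust standard errors, and do not stratify it by patient.
- Compare complications with mid-p McNemar and a confidence interval for the paired difference.

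The cost is a few sentences of wording and minor programming, possibly outside SPSS 19. No extra data or visits are needed. The change aligns the analysis with the design and endpoint, but does not cure the scarcity of failures. With 25 pairs the interval stays wide whichever method is used.

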**Discussion:**

The current study will explore the implant survival rates, safety, reliability, effectiveness, and practicability of the modified MSFE procedure. Moreover, the extent of osteogenesis on the sinus floor will also be assessed. The results of this trial will provide strategies for the modified MSFE procedure to achieve ideal clinical outcomes.

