### Challenges

Because we plan to elevate the Schneider’s membrane with the tooth/teeth on site, it will be more difficult to keep the membrane intact during the lifting process, especially if the sinus floor is proximal to the root apex and, thus, full of “lumps.” Evaluations, including CBCT analysis, should be carefully conducted before the procedure. Operators should be skilled, so that the membrane can be totally stripped along the contour of the floor. Fixing methods should be prepared beforehand as a back-up plan in case of perforation.

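### Complications are tested only by a two-sided chi-square test at p < 0.05; with 25 sides per arm, a non-significant result could not support a statement that the modified lift is as safe as the standard one

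*Protocol article*

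**What the plan says.** The Statistical analysis section of the protocol article states: "The incidence of complications will be compared using the *χ*^2^ test". The same section sets the general decision rule: "Two-sided probability (*p*) values of < 0.05 will be considered statistically significant". It attaches no margin, confidence interval or upper bound to any complication. It does plan absolute and relative frequencies.

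Three other places give this choice its weight:

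- The Discussion paragraph of the Abstract makes safety an aim: "The current study will explore the implant survival rates, safety, reliability, effectiveness, and practicability of the modified MSFE procedure".
- The Secondary parameters section lists perforation of the Schneiderian membrane among the complications.
- The Challenges section says of lifting the membrane with the teeth in place that "it will be more difficult to keep the membrane intact during the lifting process".

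The design is split-mouth ("The two sides of each patient will be randomly divided into two groups"). The Sample size section works from five-year implant survival and ends: "we further enlarged the sample size to 25 patients (50 sites) for this trial". That is 25 sides per arm, paired within patient.

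**The concern.** A test of difference can show that two rates differ. It cannot show that one is acceptably close to the other. The protocol itself gives a reason to expect more membrane damage on the test side, and this is the outcome where a reader will look for reassurance. The size was set on another outcome, so nothing ensures that the complication test can find an excess that matters.

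The trial is meant to guide periodontists on whether to adopt the procedure. If the report shows a non-significant complication comparison without an interval, it could be taken as reassurance that the data do not give.

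**Working it through.** **Inputs.** From the article: 25 patients, one test and one control side each; chi-square test; two-sided 5% level. The article gives no perforation rate, so control rates of 5–30% are assumed.

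**The plan's own figure.** There is no power or precision figure for complications. The only size calculation is for implant survival. With equal allocation (Q1 = Q2 = 0.5, assumed) and σ/δ = 5.0/5.0 = 1, the printed formula gives (1/0.5 + 1/0.5) × (1.960 + 1.282)² = 42.03 sites at two-sided 5% and 90% power. That does not reproduce the stated 32 sites. It is a separate matter, and the check below takes the final 25 patients as given.

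**Step 1: what counts as significant.** For x control and y test events with n = 25 per arm and m = x + y, Pearson's statistic is

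X² = 2n(xn − yn)² / [n²·m·(2n − m)] = 50(x − y)² / [m(50 − m)], compared with 3.84.

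- 2 vs 7 (8% vs 28%): 50 × 25 / (9 × 41) = 1250/369 = 3.39, p ≈ 0.07. Not significant.
- 2 vs 8: 50 × 36 / (10 × 40) = 4.50, p ≈ 0.03. Significant.
- 5 vs 11 (20% vs 44%): 50 × 36 / (16 × 34) = 3.31, p ≈ 0.07. Not significant.
- 5 vs 12: 50 × 49 / (17 × 33) = 4.37, p ≈ 0.04. Significant.

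This step needs no assumed underlying rate.

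**Step 2: power.** Power is the sum, over all pairs (x, y) that the test calls significant, of Bin(x; 25, p_control) × Bin(y; 25, p_test), with the arms treated as independent.

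| Control → test | Change | Pearson | Fisher |
|---|---|---|---|
| 5 → 10% | doubled | 8% | 1% |
| 10 → 20% | doubled | 17% | 9% |
| 15 → 30% | doubled | 26% | 15% |
| 20 → 40% | doubled | 35% | 23% |
| 25 → 50% | doubled | 48% | 36% |
| 30 → 60% | doubled | 62% | 51% |
| 5 → 15% | tripled | 21% | 7% |
| 10 → 30% | tripled | 45% | 31% |
| 15 → 45% | tripled | 67% | 53% |
| 20 → 60% | tripled | 87% | 79% |
| 25 → 75% | tripled | 97% | 95% |

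Power crosses 50% for a doubling at a control rate of about 26% (Pearson) or 30% (Fisher). For a tripling it crosses at about 11% (Pearson) or 14% (Fisher).

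**Step 3: does the pairing change this?** By simulation with a within-patient correlation of 0.3, Pearson power falls slightly: 13% for 10 → 20%, 44% for 10 → 30% and 33% for 20 → 40%. McNemar's test respects the pairing. Across its exact and asymptotic forms and correlations of 0 to 0.3, its power is 6–20% for 10 → 20%, 22–42% for 20 → 40% and 28–55% for 10 → 30%. At 25 → 50% it is 32–55%. A paired test is the right one for the design, but it does not make a doubling reliably detectable.

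**Step 4: what an interval would show.** Newcombe 95% limits for the difference, unpaired for illustration, have upper ends of +17.9 points with 2 vs 2 events, +27.5 with 2 vs 4, and +22.1 with 5 vs 5. Equal observed counts therefore still leave a large excess open. These widths depend on the counts and ignore the pairing.

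**The case against.** The strongest reply is that the article nowhere says p ≥ 0.05 will be read as equal safety. A reader might infer such a rule, but the text does not support it. The Abstract speaks of exploring safety, complications are one of seven secondary parameters, and the Objective and hypothesis section does not name them among the outcomes expected to be similar. This stands. The point is that the named method cannot support a safety statement, not that the protocol has promised to make one.

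A reader might also infer that safety is judged by the chi-square test alone. It is not. Frequencies by group are planned. Under Data monitoring, a committee follows adverse events, sees interim analyses and may stop the trial for harm. Under Harms, surgical failures and adverse events go to that committee at once. But none of these provisions states a numerical limit or an interval, so they do not fill the gap.

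A third tempting reading is that a tripled rate would usually be missed whatever the base rate. The table contradicts it: from a 15% control rate upward, a tripling is found more often than not. Nor do the documents set a power standard for complications. The only type II error stated is 0.10, for implant survival.

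Finally, intervals for a secondary outcome are often left to an analysis plan, and low power for harms is common in a trial of this size. Both are fair. However, the article does not stay silent on method. It fixes a test, and that test suits neither the safety aim nor the paired design, although paired tests are specified for other outcomes in the same section.

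**Conclusion.** The concern holds in limited form. Under the stated test with 25 sides per arm, a doubled perforation rate would more often be non-significant than significant at assumed control rates of 5–25%. This is clear at 5–20% (Pearson power 8–35%) and close to even at 25% (48%). A tripled rate would usually be missed only where the control rate is below about 11–14%. The boundary depends on the test used, and asymptotic McNemar with correlation 0.3 reaches 55% at 10 → 30%.

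The power figures rest on assumed rates and on all 25 pairs being available. The 2 vs 7 example needs neither an assumed rate nor a power standard, only Pearson's test applied to 25 sides per arm. A non-significant comparison would therefore be no basis for calling the modified lift as safe. This is a moderate point about method and interpretation on a stated aim, and does not touch the implant-survival hypothesis.

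**What to change.** In the Statistical analysis section, replace the chi-square sentence for complications with estimation. For membrane perforation first, and then for each other listed complication, report the test-minus-control paired risk difference with a 95% confidence interval suited to paired proportions, such as Newcombe's paired method or Tango's. Any p-value should come from a paired test and stand beside the interval. Add that safety conclusions rest on the upper limit, and that p ≥ 0.05 is not evidence of equal safety.

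Do not write a fixed excess, such as 17–22 points, into the plan. That range comes from assumed 10–20% rates and an unpaired, zero-correlation width: 1.96 × √(2 × 0.1 × 0.9/25) = 0.166 and 1.96 × √(2 × 0.2 × 0.8/25) = 0.222.

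The cost is a few sentences, with no new patients, data or procedures. The real price is that a wide upper limit will let the trial claim less on safety.
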